**NOTE: If more than 50% of items in the scale are missing, a domain score should not be computed for that domain.**

Psychosocial Health Summary Score = sum of items in emotional functioning, social functioning, and school functioning scales / (number of items answered)

Physical Health Summary Score = Physical Functioning Scale score (as shown above)

Total score: Sum of all the items / (number of items answered)

### **PedsQL for ages 8-12 years**

#### Physical Functioning (problems with...)

- Walking more than one block: Never=100, Almost Never=75, Sometimes=50, Often=25, Almost Always=0
- Running: Never=100, Almost Never=75, Sometimes=50, Often=25, Almost Always=0
- Participating in sports activity or exercise: Never=100, Almost Never=75, Sometimes=50, Often=25, Almost Always=0
- Lifting something heavy: Never=100, Almost Never=75, Sometimes=50, Often=25, Almost Always=0
- Taking a bath or shower by him or herself: Never=100, Almost Never=75, Sometimes=50, Often=25, Almost Always=0
- Doing chores around the house: Never=100, Almost Never=75, Sometimes=50, Often=25, Almost Always=0
- Having hurts or aches: Never=100, Almost Never=75, Sometimes=50, Often=25, Almost Always=0
- Low energy level: Never=100, Almost Never=75, Sometimes=50, Often=25, Almost Always=0

#### Emotional Functioning (problems with...)

- Feeling afraid or scared: Never=100, Almost Never=75, Sometimes=50, Often=25, Almost Always=0
- Feeling sad or blue: Never=100, Almost Never=75, Sometimes=50, Often=25, Almost Always=0
- Feeling angry: Never=100, Almost Never=75, Sometimes=50, Often=25, Almost Always=0
- Trouble sleeping: Never=100, Almost Never=75, Sometimes=50, Often=25, Almost Always=0
- Worrying about what will happen to him or her: Never=100, Almost Never=75, Sometimes=50, Often=25, Almost Always=0

#### Social Functioning (problems with...)

- Getting along with other children: Never=100, Almost Never=75, Sometimes=50, Often=25, Almost Always=0
- Other kids not wanting to be his or her friend: Never=100, Almost Never=75, Sometimes=50, Often=25, Almost Always=0
- Getting teased by other children: Never=100, Almost Never=75, Sometimes=50, Often=25, Almost Always=0
- Not able to do things that other children his or her age can do: Never=100, Almost Never=75, Sometimes=50, Often=25, Almost Always=0
- Keeping up when playing with other children: Never=100, Almost Never=75, Sometimes=50, Often=25, Almost Always=0

#### School Functioning (problems with...)

- Paying attention in class: Never=100, Almost Never=75, Sometimes=50, Often=25, Almost Always=0
- Forgetting things: Never=100, Almost Never=75, Sometimes=50, Often=25, Almost Always=0
- Keeping up with schoolwork: Never=100, Almost Never=75, Sometimes=50, Often=25, Almost Always=0

- Missing school because of not feeling well: Never=100, Almost Never=75, Sometimes=50, Often=25, Almost Always=0
- Missing school to go to the doctor or hospital: Never=100, Almost Never=75, Sometimes=50, Often=25, Almost Always=0

The scores are derived as follows:

Mean Physical Functioning=sum of all physical function scores / (number of items answered)

Emotional Functioning=sum of all emotional functioning scores / (number of items answered)

Social Functioning=sum of all social functioning scores / (number of items answered)

School Functioning=sum of all school functioning scores / (number of items answered)

**NOTE: If more than 50% of items in the scale are missing, a domain score cannot be computed for that domain.**

Psychosocial Health Summary Score = sum of items in emotional functioning, social functioning, and school functioning scales / (number of items answered)

Physical Health Summary Score = Physical Functioning Scale score (as shown above)

Total score: Sum of all the items / (number of items answered)

### **PedsQL for ages 13-18 years**

#### Physical Functioning (problems with...)

- Walking more than one block: Never=100, Almost Never=75, Sometimes=50, Often=25, Almost Always=0
- Running: Never=100, Almost Never=75, Sometimes=50, Often=25, Almost Always=0
- Participating in sports activity or exercise: Never=100, Almost Never=75, Sometimes=50, Often=25, Almost Always=0
- Lifting something heavy: Never=100, Almost Never=75, Sometimes=50, Often=25, Almost Always=0

- Taking a bath or shower by him or herself: Never=100, Almost Never=75, Sometimes=50, Often=25, Almost Always=0
- Doing chores around the house: Never=100, Almost Never=75, Sometimes=50, Often=25, Almost Always=0
- Having hurts or aches: Never=100, Almost Never=75, Sometimes=50, Often=25, Almost Always=0
- Low energy level: Never=100, Almost Never=75, Sometimes=50, Often=25, Almost Always=0

#### Emotional Functioning (problems with...)

- Feeling afraid or scared: Never=100, Almost Never=75, Sometimes=50, Often=25, Almost Always=0
- Feeling sad or blue: Never=100, Almost Never=75, Sometimes=50, Often=25, Almost Always=0
- Feeling angry: Never=100, Almost Never=75, Sometimes=50, Often=25, Almost Always=0
- Trouble sleeping: Never=100, Almost Never=75, Sometimes=50, Often=25, Almost Always=0
- Worrying about what will happen to him or her: Never=100, Almost Never=75, Sometimes=50, Often=25, Almost Always=0

#### Social Functioning (problems with...)

- Getting along with other teens: Never=100, Almost Never=75, Sometimes=50, Often=25, Almost Always=0
- Other teens not wanting to be his or her friend: Never=100, Almost Never=75, Sometimes=50, Often=25, Almost Always=0
- Getting teased by other teens: Never=100, Almost Never=75, Sometimes=50, Often=25, Almost Always=0
- Not able to do things that other teens his or her age can do: Never=100, Almost Never=75, Sometimes=50, Often=25, Almost Always=0

- Keeping up when playing with other teens: Never=100, Almost Never=75, Sometimes=50, Often=25, Almost Always=0

School Functioning (problems with...)

- Paying attention in class: Never=100, Almost Never=75, Sometimes=50, Often=25, Almost Always=0
- Forgetting things: Never=100, Almost Never=75, Sometimes=50, Often=25, Almost Always=0
- Keeping up with schoolwork: Never=100, Almost Never=75, Sometimes=50, Often=25, Almost Always=0
- Missing school because of not feeling well: Never=100, Almost Never=75, Sometimes=50, Often=25, Almost Always=0
- Missing school to go to the doctor or hospital: Never=100, Almost Never=75, Sometimes=50, Often=25, Almost Always=0

The scores are derived as follows:

Mean Physical Functioning=sum of all physical function scores / (number of items answered)

Emotional Functioning=sum of all emotional functioning scores / (number of items answered)

Social Functioning=sum of all social functioning scores / (number of items answered)

School Functioning=sum of all school functioning scores / (number of items answered)

**NOTE: If more than 50% of items in the scale are missing, a domain score should not be computed for that domain.**

Psychosocial Health Summary Score = sum of items in emotional functioning, social functioning, and school functioning scales / (number of items answered)

Physical Health Summary Score = Physical Functioning Scale score (as shown above)

Total score: Sum of all the items / (number of items answered)

### **9.5. Analysis methods – primary outcome(s)**

The outcome will be presented as number of URTI-related relapses along with percentage using the modified ITT cohort.

An adjusted risk difference and relative risk along with the respective 95% confidence intervals will be estimated using binomial models with the identity and log link respectively. Statistical significance of the treatment group parameter will be determined from the p-value generated by the model. The number needed to treat will also be provided.

See section 9.1 for covariate adjustment and model convergence.

### **9.6. Analysis methods – secondary outcomes**

The number of participants experiencing any relapse (i.e. both URTI-related and non URTI-related relapses), the number of participants having an escalation of background immunosuppressant therapy and the number of participants having a reduction of background immunosuppressant therapy will be presented and analysed as per the primary outcome measure.

The rate of URTI-related relapses and rate of any relapse will be presented in the first instance as numbers of participants who have a relapse with the respective percentage, and in the second instance as a median and IQR. An adjusted incidence rate ratio with 95% confidence interval will be estimated using a Poisson regression model. An offset for the length of time the participant was in the trial will be included in the model. Statistical significance of the treatment group parameter will be determined from the p-value generated by the model.

The cumulative dose of prednisolone received over the 12 month period will be presented as means with standard deviations and ranges. Adjusted mean differences along with 95% confidence intervals will be estimated using a linear regression model. Statistical significance of the treatment group parameter will be determined from the p-value generated by the model.

Adverse effect data will be tabulated at each time point (3, 6, 9 and 12 months) with statistical significance determined by a chi-squared or Fisher's exact test (as appropriate). We will also assess whether or not each adverse event occurred over the whole trial period by assessing all the 3, 6, 9 and 12 month data collectively.

Quality of life measures are taken at multiple time points, as is the Achenbach Behaviour Checklist Scores. Means and standard deviations will be summarised at each time point. Data will be analysed using mixed effect repeated measures models with the minimisation variable and the baseline questionnaire score included in the model as covariates. Time will be included as a continuous variable in the model. In the initial model, a treatment by time cross-term will be included in the model. If this is not significant, it will be considered that the treatment effect

is constant over time, and models without the treatment by time cross-term will be fitted. Adjusted mean differences between groups will be presented alongside the respective 95% confidence interval.

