It is expected that there will be relatively even representation of subjects across the four background therapy groups (no background immunosuppressive therapy, long term maintenance prednisolone therapy, long term maintenance prednisolone therapy plus other immunosuppressive therapies, other immunosuppressive therapies alone), but this will be monitored during the trial. There is no evidence to suggest that the incidence of URTI is different with any one treatment regimen compared with the others, or that the likelihood of URTI precipitating a relapse of nephrotic syndrome differs according to this background immunosuppressant therapy.

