## **9. Analysis methods**

### **9.1. Covariate adjustment**

In the first instance, intervention effects between groups for all outcomes will be adjusted for the minimisation parameter listed in section 4.6. Other covariate adjustment will be baseline values for parameters where available (e.g. an analysis of questionnaire scores will also include the baseline score as a covariate in the model).

If covariate adjustment is not possible (e.g. the model does not converge), the minimisation variable covariate will be removed from the model, but where applicable adjustment for baseline values will still be made. If the model still does not converge, unadjusted estimates will be produced, and it will be made clear in the final report why this occurred (e.g. not possible due to low event rate/lack of model convergence).

If the log-binomial model fails to converge, a Poisson regression model with robust standard errors will be used to estimate the same parameters. If this also fails to converge, unadjusted estimates will be produced from the log-binomial model. It will be made clear in the final report why this occurred (e.g. not possible due to low event rate/lack of model convergence).

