#### **Incidence of Escalation/Reduction of Background Immunosuppressant Therapy:**

The background treatment regimen is collected at each of the follow up time points. Data on second line immunosuppressants is also collected (ciclosporin, tacrolimus, levamisole, mycophenolate mofetil, mycophenolate sodium, azathioprine, cyclophosphamide and rituximab). The background treatment regime is categorised into the following four categories:

1. No long-term alternate day prednisolone or other long-term immunosuppressive therapies
2. On long-term alternate day prednisolone only
3. On both long-term alternate day prednisolone and other long-term immunosuppressive therapies
4. On other long-term immunosuppressive therapies only

The background treatment regimen and second line immunosuppressant information will be used in the following way to calculate escalation/reduction of background immunosuppressant therapy:

*Escalation will be computed based as per the following criteria –*

- If a patient is in category 1 from the background treatment regime at previous visit and then at a following time-point is in category 2, 3 or 4 of the background treatment regime then this is considered as an escalation.
- If a patient is in category 2 from the background treatment regime at previous visit and then at a following time-point is in category 3 or 4 of the background treatment regime then this is also considered as an escalation.
- If a patient is in category 4 from the background treatment regime at previous visit and then at a following time-point is in category 3 of the background treatment regime then this is also considered as an escalation.
- If the participant is not on cyclophosphamide or rituximab at previous visit but are then given cyclophosphamide or rituximab at the following time-point then this is also considered as an escalation.
- If participant has an addition of any immunosuppressant (e.g. addition of ciclosporin) in between follow up visits then this is considered an escalation.
- If the participant has a change in medication from Levamisole to either Tacrolimus, Ciclosporin or Mycophenolate then this is also considered as an escalation.

*Reduction will be computed based as per the following criteria –*

- If a patient is in category 3 from the background treatment regime at previous visit and then at a following time-point is in category 4, 2 or 1 of the background treatment regime then this is considered as a reduction.

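### Reduction of background therapy has no at-risk denominator, so a sparse no-therapy stratum pulls the regimen-adjusted risk difference towards zero

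*Combined protocol and SAP*

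**What the plan says.** SAP 9.6 treats reduction as a binary secondary outcome: "the number of participants having a reduction of background immunosuppressant therapy will be presented and analysed as per the primary outcome measure". Under SAP 9.5 the risk difference and relative risk are "estimated using binomial models with the identity and log link respectively", significance comes from the model's p-value, and an NNT is given. SAP 9.1 adds that "intervention effects between groups for all outcomes will be adjusted for the minimisation parameter listed in section 4.6"; that parameter is the four-level background regimen. The population (SAP 5.3) is every child with at least one URTI. Nothing limits the reduction outcome to children with therapy to reduce.

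The first regimen category in SAP 9.4 is "No long-term alternate day prednisolone or other long-term immunosuppressive therapies". On its share, protocol 4.2 says: "It is expected that there will be relatively even representation of subjects across the four background therapy groups". SAP 9.4 scores reduction by comparing each time point with the one before, not with randomisation.

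If adjustment fails, SAP 9.1 provides that "the minimisation variable covariate will be removed from the model". For the log-binomial model it also offers Poisson regression with robust standard errors.

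The outcome's definition differs between documents. SAP 9.4 counts a step down in category or loss of an agent (cyclophosphamide and rituximab excepted). Protocol 4.23.2 describes reduction as stopping maintenance prednisolone, while the synopsis objective also gives stopping ciclosporin as an example.

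**The concern.** A child randomised on no therapy starts with nothing to reduce. To count, the child must first be escalated and then stepped down within 12 months. Protocol 4.10 limits both steps: a new agent is added only after two or more relapses in six months or for unacceptable adverse effects, and therapy is discontinued only after six relapse-free months or for unacceptable adverse effects. Events in this stratum should therefore be few.

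An identity-link model with regimen as covariate fits one common risk difference to all four strata. A stratum with a risk near zero in both arms has very small binomial variance and says the difference is near zero, so it dominates the fit.

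At stake is secondary objective vi, whether the intervention increases reduction of background therapy. The planned risk difference and NNT could understate an effect that exists among the children who can have one. Those events that do occur in the stratum are reversals of in-trial escalations. Protocol 4.29 expects more intensification on placebo if the treatment works, so such reversals would tend to credit the placebo arm.

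**Working it through.** **Inputs.** The documents state no reduction rate, so there is no planned figure for this outcome to reproduce. Numbers per stratum come from the primary sample size (SAP 4.7), which does reproduce. For 50% v 32.5%, two-sided 0.05, 80% power: n per arm = [1.960√(2×0.4125×0.5875) + 0.842√(0.25+0.2194)]² / 0.175² = 123.03, so 124, or 248 in total (stated 250). Then 250/0.70 = 357.1, so 358 (stated 360). With 250 analysed in eight equal cells, n = 250/8 = 31.25 per arm per stratum. With equal strata, n does not affect the point estimates below.

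**Assumption.** Reduction risk is 20% on placebo and 35% on active in each of the three strata with therapy at randomisation. At-risk difference: 15.0 points. Crude difference over all children with an empty fourth stratum: 0.75 × 15 = 11.25 points.

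**Empty no-therapy stratum.** For a common difference d ≥ 0, this stratum's likelihood is maximised with placebo risk 0 and active risk d. It contributes n·ln(1−d), with slope −n = −31.25 at d = 0. Each other stratum has slope n(p1−p̄)/[p̄(1−p̄)] at d = 0, where p̄ is the mean of the two risks:
- 20% v 35%: p̄ = 0.275; 31.25×0.075/0.1994 = 11.76; three strata give 35.3. This barely exceeds 31.25, so the maximum lies just above zero. One Newton step, with curvature 3×31.25/(2×0.1994) + 31.25 = 266, gives (35.3−31.25)/266 = 0.015.
- 20% v 30%: p̄ = 0.25; 3×31.25×0.05/0.1875 = 25.0. This is below 31.25, so the estimate is exactly 0 although the at-risk difference is 10 points.

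Full maximisation gives 1.5 points for 20% v 35% (likelihood-ratio chi-squared 0.06, p = 0.80), against 15.0 in the three at-risk strata alone (5.34, p = 0.02). For 20% v 40%, 20.0 points becomes 5.4.

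**Events in the no-therapy stratum** (20% v 35% elsewhere; by maximum likelihood, read to about 0.1 point):

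| No-therapy stratum, placebo / active | Crude RD | Adjusted RD | NNT = 1/adjusted RD |
|---|---|---|---|
| 0% / 0% | 11.3 | 1.5 | 65 |
| 3% / 3% | 11.3 | 6.1 | 16 |
| 6% / 6% | 11.3 | 7.8 | 13 |
| 10% / 10% | 11.3 | 9.1 | 11 |
| 6% / 3% | 10.5 | 5.4 | 18 |

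For comparison, the at-risk NNT is 1/0.15 = 6.7 and the crude NNT is 1/0.1125 = 8.9. If a share of 10% to 50% escalate and 10% to 50% of those later step down, the stratum risk is between 0.1×0.1 = 1% and 0.5×0.5 = 25%, so all the rows with events are plausible.

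**Share of the stratum.** With no events there, shares of 5%, 10%, 15%, 25% and 35% give adjusted differences of 12.7, 10.2, 7.5, 1.5 and 0.0 points.

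**Relative risk and convergence.** Whole-number counts of 6/32 v 11/32 in three strata and 0/32 v 0/32 in the fourth were fitted in Python statsmodels. The identity-link fit converged at 0.024 (SE 0.025), against 0.117 (SE 0.049) unadjusted. The log-link treatment effect was exp(0.606) = 1.83 = 11/6, the at-risk relative risk; only the empty stratum's own intercept was not estimable. The same data give z = 0.024/0.025 = 0.96 for the risk difference (an SE from a boundary fit, so indicative only) and 0.606/0.255 = 2.38 for the relative risk. SAP 9.5 does not say which governs. The identity-link fit reported convergence in about 93% of 60 simulated trials with an empty stratum.

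**The case against.** The strongest reply is that SAP 9.4 scores visit to visit, so the no-therapy stratum need not be empty. These children had at least two relapses in the previous year, and protocol 4.9 lets maintenance prednisolone be recommenced after relapse treatment at the investigator's discretion. Moving from no therapy to prednisolone and back would count. This stands. A reader might infer that reduction is impossible in these children and that the adjusted risk difference must collapse; the documents do not support that. With even 3% of events per arm the estimate is attenuated rather than lost.

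Second, the relative risk is also planned, and an empty stratum leaves it intact. This stands, so it would be wrong to infer that both models fail.

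Third, the crude difference over the whole mixed population is a legitimate marginal effect, and objective vi counts subjects in that population. This also stands. It does not defend the adjusted difference, which falls below the crude one in every row of the table.

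Fourth, the SAP 9.1 fallback might rescue the analysis. It offers non-convergence only as an example and mentions low event rates as a possible reason for unadjusted estimates, so an analyst could invoke it. But no rule ties it to a sparse stratum, and a fit that reports convergence would normally be kept. The trial will use SAS and Stata, which were not tested, so whether it triggers remains open.

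**Conclusion.** The point holds in conditional form. As written, the SAP applies a common additive risk difference, adjusted for regimen, to an outcome that one regimen level can reach only by first being escalated in the trial. If events there are few, the risk difference is pulled towards zero and the NNT inflated. Under 20% v 35% elsewhere and a quarter of children on no therapy, a 15-point at-risk difference is reported as about 1.5 points with no events in that stratum and about 6 to 9 points with 3% to 10% in each arm, against 11.3 crude.

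The size rests on assumed reduction rates and on the protocol's expectation, not an observation, of an even spread over regimens. It affects the risk difference, its p-value and the NNT for one secondary outcome. The primary outcome is untouched.

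**What to change.** - **SAP 9.6:** restrict the reduction outcome to modified-ITT children on background therapy at randomisation, adjust for the remaining strata, and describe the no-therapy stratum separately. If all children are kept, report a standardised (marginal) risk difference instead of the identity-link coefficient, and derive the NNT from it.
- **SAP 9.4:** score reduction against the regimen at randomisation, so that reversing an in-trial escalation does not count.
- **Definition:** reconcile SAP 9.4 with protocol 4.23.2 and the synopsis objective. Under the narrower wording (stopping maintenance prednisolone), children on other immunosuppressants alone also have nothing to stop at baseline, so the at-risk group must follow the agreed definition.

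This is a wording change that needs no new data. Because the restriction uses the baseline minimisation factor, it keeps the randomised comparison. The cost is about a quarter fewer children for this outcome (0.75 × 250 = 187.5, so about 188), or about half if the narrower definition is adopted, and in-trial reversals would be reported only descriptively.

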The most recent and largest study was performed in 100 Indian children recently diagnosed with frequently relapsing SSNS 'eligible for therapy with long-term alternate day prednisolone with or without levamisole' [Gulati *et al*, 2011]. Children were recruited in stable remission, having received alternate day prednisolone 1.5mg/kg for 4 weeks, and then tapered by 0.25mg/kg every 2 weeks, until a dose of 0.5-0.75mg/kg on alternate days was reached. If a dose of prednisolone greater than 1mg/kg on alternate days was required, then levamisole was added. Children were randomised (stratified according to whether they received levamisole ( $n=32$ ) or not ( $n=68$ )) to either daily prednisolone for 7 days or to remain on alternate day prednisolone in an unblinded manner at the time of development of URTI (defined as fever  $>38^{\circ}\text{C}$ , rhinorrhoea or cough for  $>1$  day and diarrhoea for  $>2$  days). Children were reviewed every 2 months for a total of 12 months. The primary endpoint was the incidence of infection-associated relapse, with secondary

endpoints of infection frequency and type and cumulative dose of prednisolone. Patients exited the study if there were 2 or more relapses in any 6 month period. Daily prednisolone therapy at the time of URTI resulted in a reduction in the incidence of infection-associated relapse (0.7 vs. 1.4; rate difference: 0.7, 95% confidence interval (CI): 0.3 to 1.1;  $p < 0.01$ ) and the overall relapse rate (0.9 vs. 1.8; rate difference: 0.9, 95% CI: 0.4 to 1.4;  $p < 0.0001$ ). Whilst not powered to do so, a sub-analysis showed that this difference was lost in those receiving levamisole. Nineteen children in the daily prednisolone group vs. 7 in the alternate day group remained relapse-free over the entire 12 month study period ( $p = 0.03$ ). There was no difference in cumulative prednisolone dose between the two arms. More infections occurred in the daily prednisolone group (226 vs. 161;  $p = 0.04$ ), though no difference was detected in height SDS, Cushingoid features, cataract or serious infection. A total of 6 children (2 in daily steroid group) exited the study because of treatment failure necessitating treatment with cyclophosphamide or calcineurin inhibitors.

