#### **4.29 Statistical Analysis**

The Statistical Analysis Plan describes the planned analyses for PREDNOS 2 in full detail. A summary of the main analysis methods are described here.

The primary endpoint is the first URTI-related relapse of nephrotic syndrome (URT-related relapse is defined as 3 days of Albustix 3+ proteinuria within 14 days of onset of an URTI) which occurs during the 12 month follow-up period. The proportion of subjects that experience an URTI-related relapse will be calculated for the two study treatment arms, and compared using a chi-squared test. Treatment effects will be expressed as relative risks with 95% confidence intervals.

This was chosen as the primary endpoint as it is hypothesised that giving daily prednisolone at time of URTI will reduce the subsequent development of disease relapse. If this hypothesis is correct, then those subjects randomised to placebo will experience more URTI-related relapses than those subjects randomised to active drug. This would mean that subjects in the placebo arm are more likely to undergo intensification of immunosuppressive therapy. This in turn would reduce the chances of the subjects in the placebo arm from having further relapses (both URTI-related and non URTI-related) which introduces bias. Therefore, all subjects will be followed-up for 12 months to also assess the relapse rates between the two treatment arms over a 12 month period as a secondary endpoint, but due to these potential biases, the primary endpoint will focus on the first URTI-related relapse. The analysis of the secondary endpoints for relapses per year will assess incidence (relapse) density rates for the two treatment arms and rate differences will be calculated for both URTI and non-URT related relapse of nephrotic syndrome over the 12 month follow-up period. Appropriate regression analysis (e.g. Poisson) will be used to compare relapse rates in the two treatment groups, should there be an imbalance in any important co-variables (e.g. URTI rates across the two study arms).

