## **9.2. Distributional assumptions and outlying responses**

Distributional assumptions (e.g. normality of regression residuals for continuous outcomes) will be assessed visually prior to analysis; although in the first instance the proposed primary method of estimation in this analysis plan will be followed. If responses are considered to be particularly skewed and/or distributional assumptions violated, the impact of this will be examined through sensitivity analysis; this will consist of transformation of responses prior to analysis (e.g. log transformation) in the first instance. If extreme values are apparent and considered to be affecting the integrity of the analysis, a sensitivity analysis consisting of removing the outlying response(s) and repeating the analysis will be performed. Output from these analyses, if performed, will be described and presented alongside the original analysis (or included, e.g. in appendices) with the excluded values clearly labelled.

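### SAP 9.6 names no robust standard error or dispersion check for the two relapse-rate outcomes, so their intervals and p-values rest on variance equalling the mean

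*Combined protocol and SAP*

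**What the plan says.** The two relapse rates are the first two secondary outcomes in SAP 4.4. SAP 9.6 specifies for both: "An adjusted incidence rate ratio with 95% confidence interval will be estimated using a Poisson regression model". It adds "An offset for the length of time the participant was in the trial will be included in the model" and "Statistical significance of the treatment group parameter will be determined from the p-value generated by the model". Under SAP 9.1 the model is adjusted for background therapy, the only minimisation variable. SAP 5.1 sets two-sided tests at 5% with 95% intervals, and SAP 5.2 makes no multiplicity correction.

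Robust errors appear once, in SAP 9.1, as the fallback when the log-binomial model for a binary outcome does not converge: "a Poisson regression model with robust standard errors will be used to estimate the same parameters".

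SAP 9.2 has a general provision: "If responses are considered to be particularly skewed and/or distributional assumptions violated, the impact of this will be examined through sensitivity analysis". The remedies it names are transformation first, and removal of outliers where extreme values matter. SAP 9.10 confines its sensitivity analyses to the primary outcome.

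Protocol 4.29 presents itself as a summary and refers to the SAP for full detail. It gives Poisson only as an example of a suitable regression, and makes regression conditional: "should there be an imbalance in any important co-variables (e.g. URTI rates across the two study arms".

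**The concern.** A child can relapse several times in 12 months. A Poisson model with its default standard error takes the variance of those counts to equal the mean, given the covariates. The documents give reasons to doubt this in both directions.

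- **Variance above the mean.** Children range from no background drug to prednisolone combined with other immunosuppression (protocol 4.2). One four-level covariate is unlikely to remove all differences in relapse risk between children.
- **Variance below the mean.** Each relapse starts a course of daily and then alternate-day prednisolone (protocol 4.9), and repeated relapses can lead to intensified therapy (protocol 4.10). Protocol 4.29 itself expects intensification to reduce later relapses.

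If the variance exceeds the mean, the intervals are too narrow and the p-values too small; if it is lower, the reverse. At stake is the calibration of two secondary comparisons, each read at 5%.

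**Working it through.** **1. The plan's own figure.** The documents state no power or sample size for the relapse rates. Their only figure is for the primary outcome (SAP 4.7): 50% vs 32.5%, 80% power, two-sided 5%. With pooled proportion 0.4125,

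n per arm = [1.96 × √(2 × 0.4125 × 0.5875) + 0.8416 × √(0.5 × 0.5 + 0.325 × 0.675)]² / 0.175² = (1.3645 + 0.5766)² / 0.030625 ≈ 123.0, rounded up to 124.

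That is 248 in total, against 250 stated. 250 / 0.70 = 357.1, so 358, against 360 stated. The figure reproduces, and 125 per arm is used below as the analysed size.

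**2. Type I error when variance = φ × mean.** The default Poisson error is too small by a factor √φ, so the real two-sided error of a nominal 5% Wald test is 2 × [1 − Φ(1.96/√φ)]. φ is not given for this trial; 0.5 to 3.0 is an assumed range. The simulation used 125 per arm, a mean of 1.0 relapse per child, equal follow-up, no covariates, 4,000 runs per row, gamma-Poisson counts for φ > 1 and binomial counts for φ < 1.

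| φ | Formula | Simulated, default error | Simulated, robust error | Correct width / Poisson width (√φ) |
|---|---|---|---|---|
| 0.5 | 0.6% | 0.5% | 5.0% | 0.71 |
| 0.8 | 2.8% | 2.8% | 5.4% | 0.89 |
| 1.0 | 5.0% | 5.3% | 5.6% | 1.00 |
| 1.2 | 7.4% | 7.4% | 5.6% | 1.10 |
| 1.5 | 11.0% | 10.5% | 5.2% | 1.22 |
| 2.0 | 16.6% | 16.3% | 5.6% | 1.41 |
| 3.0 | 25.8% | 24.8% | 5.7% | 1.73 |

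At a mean of 1.8 the pattern is the same, and the robust error stays between 5.3% and 5.7%.

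**3. What the cited studies imply for φ (protocol 3.1).**

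*The 100-child study*, 12 months, 50 per arm assumed. φ = (CI half-width / 1.96)² / [(rate₁ + rate₂)/50].

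- Infection-associated relapse, 0.7 vs 1.4, CI 0.3 to 1.1: (0.4/1.96)² / (2.1/50) = 0.04165 / 0.042 = 0.99. Allowing the CI width to be off by 0.1 through rounding: 0.76 to 1.26.
- All relapses, 0.9 vs 1.8, CI 0.4 to 1.4: (0.5/1.96)² / (2.7/50) = 0.06508 / 0.054 = 1.21. With the same rounding: 0.98 to 1.46.
- A 45/55 split in either direction gives 0.95 to 1.23 across the two outcomes.

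Those intervals may themselves have been Poisson-based, which would pull φ towards 1. The relapse-free counts are a separate check: 19/50 = 38% and 7/50 = 14%, against Poisson values exp(−0.9) = 41% and exp(−1.8) = 17%. There is no excess of relapse-free children.

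At φ of 1.0 to 1.2 the type I error is about 5% to 7%; at 1.46 it is 10.5%.

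*The 36-child study*, two years: 0.87²/2.2 = 0.34 and 1.33²/5.5 = 0.32. If the reported means are per year rather than two-year totals, the ratio for counts doubles to about 0.69 and 0.64.

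**4. URTI rate, protocol against SAP.** Protocol 4.29 makes regression depend on imbalance and names URTI rates as an example. SAP 9.1 and 9.6 always fit the regression. Their covariates are the minimisation variable and, where available, a baseline value of the outcome; the offset is time in trial. URTI rate is neither covariate nor offset in the SAP.

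**The case against.** The best case for leaving the plan alone has four parts.

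- **The SAP never says that the errors are model-based.** True; this is inferred from silence. But where the SAP wants robust errors it names them, so the default reading is the natural one.
- **The closest data sit near φ = 1.** This stands, and it limits the size of the point. That study was narrower, however: all its children were candidates for alternate-day prednisolone with or without levamisole, and children left on two relapses within six months, which truncates counts. This trial admits four background regimens and keeps following such children.
- **SAP 9.2 already covers failed assumptions.** It does require a check. Neither named remedy corrects the standard error of a Poisson count model, and SAP 9.10 lists no sensitivity analysis for these outcomes.
- **The consequence is limited.** Correct. Both outcomes also have binary counterparts analysed by binomial models (SAP 9.5 and 9.6).

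A reader might infer three stronger claims that the documents do not support.

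- *The inference is wrong whenever counts depart from Poisson, or strong overdispersion is established.* The error is small near φ = 1 and conservative below it, and no cited study shows a φ near 2.
- *The 36-child study shows Poisson intervals about 1.7 times too wide (1/√0.33 = 1.74).* That sample excluded children who did not relapse, and its time unit is unclear. On the per-year reading the factor is only about 1.2 (1/√0.69 = 1.20; 1/√0.64 = 1.25).
- *The trial will adjust for URTI rate and so overstate benefit.* The 100-child study reports "More infections occurred in the daily prednisolone group (226 vs. 161", and its rate ratio is 0.7/1.4 = 0.50 per child but (35/226)/(70/161) = 0.155/0.435 = 0.36 per infection (50 per arm assumed). But the SAP plans no such adjustment. That study was also unblinded and counted infections under a different definition, so it does not show that prednisolone changes the URTI rate as defined here.

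**Conclusion.** The point holds as a gap in specification. On the default reading, the intervals and p-values of two secondary outcomes depend on variance equalling the mean, and nothing in the SAP checks or corrects this. On the nearest evidence the likely cost is modest: a type I error of about 5% to 7%, or 10.5% at the upper end of rounding. The 11% and 17% figures belong to assumed ratios of 1.5 and 2.0. Below 1 the cost is lost precision instead. The direction cannot be settled from the documents.

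This rests on the default reading of an unqualified Poisson model and on 50 children per arm in the 100-child study. The rate-ratio estimates remain valid if the model for the mean is right. The primary outcome and its sample size are untouched. The protocol's mention of URTI rates is a wording mismatch with the SAP, not an error in the planned analysis.

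**What to change.** In SAP 9.6, state that both relapse-rate outcomes use the same Poisson model, with the time-in-trial offset and adjustment for background therapy, and robust (sandwich) standard errors. This handles variance above or below the mean, whereas a standard negative binomial model cannot represent variance below it. It needs one model option and no new data. The price is wider intervals if counts are overdispersed: by √1.2 = 1.10 (10%), √1.5 = 1.22 (22%) or √2 = 1.41 (41%). If counts are close to Poisson, little is lost.

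As a minor wording change, remove URTI rate from protocol 4.29 as an example of an imbalance that triggers regression, so that the text agrees with SAP 9.1 and 9.6. URTI counts can still be reported by arm as description.
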